## 7 ASSESSMENTS AND FOLLOW-UP

### 7.1 Duration of follow-up and schedule

An overview on study procedures are provided in the TaMoVac II Schedule (**Appendix 2**).

Participants will be required to make a minimum of 17 scheduled outpatient visits over the course of 52 weeks, with an optional extension to 18 visits over 64 weeks. Time 0 will start on the day of enrolment, which is also the day of randomisation and first immunisation.

Screening can take place up to 8 weeks (56 days) before time 0.

Immunisations will take place at weeks 0, 4, 12, 24 and 40.

Clinical safety follow up visits will be conducted 2 and 4 weeks after each immunization.

Long term immunogenicity and safety visits will be performed for a minimum of 12 weeks after the last immunization or are expected to be conducted until 24 weeks after the last immunization (optional).

Serum and peripheral blood mononuclear cells (PBMC) will be collected for immunogenicity at screening (Visit 2), enrolment (Visit 3), and weeks 14 (Visit 9), 26 (Visit 12), 28 (Visit 13), 42 (Visit 15), 44 (Visit 16) and 64 (Visit 18). Optionally the week 64 (Visit 18) immunogenicity tests will be performed at week 52 (Visit 17) if Visit 18 is not expected to be conducted.

Adverse events will be assessed during the enrolment visit following immunisation and at every visit thereafter. Routine laboratory safety parameters will be collected at screening, baseline, at every visit thereafter and at any other unscheduled visit if clinically indicated.

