## 9.3 Sample size

One hundred and eighty (180) individuals will be randomised to an active product group for the purpose of the analysis, with a further 18 individuals randomly allocated to receive saline for the purpose of blinding the laboratory and clinical staff and to reinforce the message that participants should not consider themselves protected against HIV. There will be two randomisations, the first to compare the three DNA treatment groups, each of which will have approximately 60 participants, and the second to compare two groups, namely MVA-CMDR given with CN54rgp140/GLA-AF and MVA-CMDR alone, each of which will have approximately 90 participants.

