#### ***Continuous variable (Magnitude of cellular response)***

An important difference in the magnitude of cellular responses will be defined as a doubling of mean SFC/ $10^6$  response in any CMDR pool, excluding the negative responders.

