### Statistical assumptions

Alpha will be reduced to 2.5% ( $p=0.025$ ) to adjust for multiple comparisons of the first randomisation, and will be 5% for the second randomised comparison. The following tables illustrate the power to detect a difference in a continuous variable or proportion with 60 or 90 subjects per group, using magnitude of response, and frequency of responders respectively.

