### Power to detect differences in a continuous variable:

| Increase in SFC          | Power when n=60 per group | Power when n=90 per group |
|--------------------------|---------------------------|---------------------------|
| 100% increase (doubling) | 85                        | 98                        |
| 75% increase             | 66                        | 90                        |
| 50% increase             | 38                        | 66                        |

Note: Based on  $\log_{10}$  transformed SFC, assuming a standard deviation of 0.5.

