#### **Power to detect a range of differences in a proportion:**

| Increase in absolute difference (control to group of interest) | Power when n=60 per group | Power when n=90 per group |
|----------------------------------------------------------------|---------------------------|---------------------------|
| 40% to 70%                                                     | 86                        | 98                        |
| 40% to 60%                                                     | 48                        | 77                        |
| 50% to 80%                                                     | 89                        | 99                        |
| 50% to 70%                                                     | 50                        | 78                        |

60 participants per group provides adequate power ( $\geq 85\%$ ) to detect a doubling in mean magnitude or to detect a 30% absolute difference in the proportion of responders however the latter is defined. However, there is insufficient power to detect smaller differences, which could still be clinically meaningful. Ninety participants per group also provides adequate power for detecting a 75% increase in the magnitude of immune responses.

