Prior to the main analysis, the Statistical Analysis Plan will be finalised describing the methods for comparing the groups in detail. The decision to compare the proportion of responders, or the magnitude of response, and the definition for these parameters will be informed by the full analysis of TaMoVac 01 and the results of other relevant clinical trials, with the aim of defining a 'clinically meaningful result'. Proportions will be presented with a confidence interval and groups compared using Fisher's exact test. Response magnitude will be compared between groups using rank tests.

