#### **(v) Heterologous prime boost vaccination regimes.**

In a trial which enrolled participants who had previously been primed with either DNA or Ad5 alone, the advantages of the heterologous prime boost strategy were evident, with an approximately 7 fold increase in immune responses following Ad5 boosting after DNA priming. This effect was evident in both the T-cell and B-cell compartments [22]. In the HIVIS 03 trial which recruited healthy volunteers in Tanzania, 58% of individuals receiving three injections with multiclade DNA made a positive  $\gamma$ -IFN T-cell Elispot response and this increased to ~100% after boosting twice with MVA. Interestingly, due to problems with product availability, up to 3 years elapsed between the two MVA-CMDR immunisations in this trial. There have been concerns about the dampening effects of vector-specific responses on vaccine immunogenicity and the striking T-cell and B-cell responses seen in this trial may have been due to this (impractically) drawn out schedule.

Apart from intrinsic flexibility and relatively modest manufacturing costs, the rationale for using DNA as a component of HIV vaccines stems also from a desire to induce cytotoxic T cells-responses which depend largely upon the expression of endogenous proteins. Unfortunately, the potency of DNA vaccines first described in animal models has not been realised in the clinic, and this had led to a focus on the development of methods specifically focussed on increasing the efficiency of DNA uptake by cells. Electroporation and the use of needle free devices such as the Biojector have both been shown to increase the immunogenicity of DNA although, to date, electroporation has only been shown to be effective in one clinical trial and the choice of device used is probably key to success [23]. We believe that the cumulative dose of DNA used in priming is crucial in determining the breadth and magnitude of the T-cell response (in this case 12mg given over 8 weeks). The uptake of DNA after IM administration is known to be highly inefficient (~5%) and this may be one of the explanations of the relatively poor performance of DNA vaccines in the clinic. We propose that Electroporation and the Biojector device are included in the proposed trial with the explicit aim of improving the efficiency of uptake of DNA by target cells.

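### Boost comparison of ELISpot magnitude: section 9.5.2 names a rank test without a covariate, although week-14 ELISpot is a valid baseline for the second randomisation

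*Protocol*

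**What the plan says.** - **Method.** Section 9.5.2: "Response magnitude will be compared between groups using rank tests". No covariate or stratification is named. The same paragraph leaves the detailed methods, and the choice between responder proportion and magnitude, to a later statistical analysis plan.
- **Endpoint.** Section 9.2.1.1 takes ELISpot magnitude two weeks after the final vaccination (week 42), in positive samples only.
- **Sampling.** Section 7.1 says that serum and cells "will be collected for immunogenicity at screening (Visit 2), enrolment (Visit 3), and weeks 14 (Visit 9") and at later visits. Appendix 2 marks fresh-cell ELISpot at both Visit 9 (week 14) and Visit 15 (week 42).
- **Second randomisation.** Section 5.2 places it before MVA, which is first given at week 24. It is stratified by centre, gender and first-randomisation outcome.
- **Use of the post-prime response.** Section 9.2.2.1 lists it as a secondary outcome. It has no stated role in the boost comparison.
- **Power.** Section 9.3 gives 98%, 90% and 66% at 90 per group for increases of 100%, 75% and 50%, based on log10 "transformed SFC, assuming a standard deviation of 0.5".

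**The concern.** The week-14 ELISpot comes two weeks after the third DNA dose and before any boost, so the boost allocation cannot affect it. Participants probably differ widely at that point. Appendix 9 reports that in an earlier Tanzanian trial "58% of individuals receiving three injections with multiclade DNA made a positive" ELISpot response, and that 30% responded after DNA in the Swedish trial. The randomisation strata do not capture an individual's primed response.

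If that response predicts the boosted one, a comparison that ignores it carries avoidable variance and is open to chance imbalance in priming between the boost arms. At stake is power for effects below the design target. The section 9.3 table itself puts power for a 50% increase at 66% with 90 per group.

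**Working it through.** **Inputs**
- Group size: two boost groups, "each of which will have approximately 90 participants" (section 9.3).
- Alpha: reduced for the first randomisation "and will be 5% for the second randomised comparison". Sidedness is not stated; two-sided reproduces the table.
- SD: 0.5 on log10 SFC.
- Target: "An important difference in the magnitude of cellular responses will be defined as a doubling of mean" SFC, which is log10(2) = 0.301. The table also covers log10(1.75) = 0.243 and log10(1.5) = 0.176.
- Correlation rho between week-14 and week-42 log10 SFC: **not in the protocol**; assumed over a range.

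**Step 1: reproduce the stated power.** Power = Phi(delta / (SD × sqrt(2/n)) − 1.96). The standard error is 0.5 × sqrt(2/90) = 0.0745.
- Doubling: 0.301/0.0745 = 4.04; 4.04 − 1.96 = 2.08; power 98.1% (stated 98).
- 75% increase: 0.243/0.0745 = 3.26; 3.26 − 1.96 = 1.30; power 90.3% (stated 90).
- 50% increase: 0.176/0.0745 = 2.36; 2.36 − 1.96 = 0.40; power 65.6% (stated 66).

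The stated figures reproduce.

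**Step 2: adjust for week 14.** Replace the SD by 0.5 × sqrt(1 − rho²). For example, at rho 0.5 the SD is 0.5 × sqrt(0.75) = 0.433 and the standard error 0.0645. For a 50% increase, 0.176/0.0645 − 1.96 = 0.77, giving 77.9%.

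| rho (assumed) | residual SD | +100% | +75% | +50% |
|---|---|---|---|---|
| 0 | 0.500 | 98.1 | 90.3 | 65.6 |
| 0.2 | 0.490 | 98.5 | 91.4 | 67.4 |
| 0.3 | 0.477 | 98.9 | 92.8 | 69.7 |
| 0.4 | 0.458 | 99.3 | 94.5 | 73.2 |
| 0.5 | 0.433 | 99.7 | 96.4 | 77.9 |
| 0.6 | 0.400 | 99.9 | 98.3 | 84.0 |

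**Step 3: allow for non-responders at week 14.** If non-responders share one floor value, the covariate carries less information. In a simulation with bivariate normal values, an underlying rho of 0.5 falls to 0.445 with 58% responders and to 0.37 with 30%. The Step 2 formula then gives residual SDs of 0.448 and 0.465, and about 75% and 72% power for a 50% increase. An underlying rho of 0.3 falls to 0.267 and 0.222, giving about 69% and 68%.

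**Step 4: rank scale.** The table's powers are those of a normal-theory test. With a rank efficiency of 0.955 (n = 90 × 0.955 = 86), power for a 50% increase is 63.6% unadjusted, 67.7% at rho 0.3 and 76.0% at rho 0.5. The gain is of similar size.

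**Step 5: positive samples only.** Ninety per arm is an upper bound. If 90% or 80% of samples were positive (assumed), unadjusted power for a 50% increase would be 61.1% or 56.1%.

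**The case against.** The strongest reply is that covariate choice belongs in the statistical analysis plan, to which section 9.5.2 expressly defers the detail. The section does not call the test unadjusted, and a rank analysis of covariance is itself a rank method. This largely stands. A reader might infer that the protocol discards the week-14 information, but it only names a method with no covariate and leaves room to add one. The point survives as a recommendation because a method is named and the post-prime response is given only a descriptive role.

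A reader might also take the statement in section 9.3 that "there is insufficient power to detect smaller differences, which could still be clinically meaningful" as an admission about the boost comparison. In sequence, it follows a sentence about 60 per group and precedes one saying that 90 is adequate for a 75% increase, so it reads as being about the first randomisation. Week 14 cannot be a baseline there, because it follows DNA allocation. For the boost comparison, the only support is the 66% in the table, for an effect below the target.

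It is tempting to adjust the CN54rgp140 IgG titre in the same way. The protocol points against this. Section 9.5.2 titrates only samples with detectable antibody, and Appendix 9 reports Env antibody in only 5% after three DNA doses plus one MVA boost. The 58% and 30% are cellular response rates.

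Three further limits stand:
- Spread in response at week 14 does not establish correlation with week 42.
- The gain is measured against no adjustment. Part of it may already come from an analysis that respects the strata, and the extra gain over that is not estimated.
- The restriction to positive samples is applied after randomisation, and a baseline covariate does not cure that.

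**Conclusion.** The point holds as a minor improvement, confined to ELISpot magnitude in the second randomisation. Week-14 ELISpot is measured by the same assay, precedes the boost and is already scheduled, so adjusting for it is valid.

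For a 50% increase, power would rise from 66% to about 70-78% at an assumed correlation of 0.3 to 0.5, and by about 2 points at 0.2. Flooring of week-14 non-responders pulls the result toward the lower part of that range or slightly below it. For the target doubling the gain is under 2 points. These figures assume 90 analysable participants per arm and a log10 SD of 0.5.

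The named rank test is valid, the comparison is not biased, and the stated power is correct. The benefit is precision for smaller effects and protection against chance imbalance in priming.

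**What to change.** Before unblinding, prespecify the following for the boost comparison of ELISpot magnitude:
- A rank analysis of covariance (Quade), or an analysis of covariance on log10 values, of week-42 SFC with week-14 SFC as covariate.
- A floor value plus a responder indicator for week-14 non-responders, and a missing-indicator where the week-14 assay is absent or failed, so that no one is dropped.
- The randomisation strata (centre, gender, DNA group) in the same model.
- The unadjusted rank test as a sensitivity analysis.

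Leave the CN54rgp140 IgG comparison without this covariate.

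The cost is wording in the statistical analysis plan. No sample, visit or assay is added, and the sample size does not change.

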### 9.5.3 Safety variables

The original verbatim terms used by the investigator to identify AEs in the CRFs will be coded using an appropriate medical coding scheme (MedDRA). In all summaries, if a participant reports the same system organ class or preferred term more than once then the worst severity and worst relationship to trial vaccine will be taken. Discrepancies between diary card and CRF reports will be queried and resolved. It is assumed that the grade assigned by the clinician is more accurate, and this will be the grade reported in the tables. If the diary card grade is worse, this will be foot-noted.

All safety end-points will be graded by the Clinical Investigators and reviewed by the Trial Management Group. In the unlikely event that the TMG cannot reach consensus about grade and relationship to study product, an expert Endpoint Panel will be assembled.

Safety outcomes will be reported overall with proportion and 95% confidence interval, and by group and time-point, and by relationship to study product.

For the primary analysis of safety endpoints (as defined in **section 9.2.1**), results will be expressed as a proportion with confidence interval, and groups compared using Fisher's exact test.

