**Table 2 Solicited adverse events**

| Type                             | Event                                                                                                                                                         |
|----------------------------------|---------------------------------------------------------------------------------------------------------------------------------------------------------------|
| Local AEs
(immunisation site) | Local Pain
Local Itching
Warmth
Redness in cm
Swelling (soft) in cm
Induration (hard) in cm
Blisters (blood or clear) in cm
Papule in cm |
| Systemic
Clinical AEs         | Temperature
Chills
Myalgia/flu-like general muscle aches
Aching joints
Malaise (excess fatigue)
Headache
Nausea
Vomiting                 |
| Systemic
Laboratory AEs       | Creatinine, ALT, total and direct bilirubin, glucose
Hb, total WBC, neutrophils, lymphocytes, platelets                                                    |

The events will be **graded** according to the toxicity table in **Appendix 8**.

**Relationship** will be recorded in the immunisation CRF but not on the diary card, on the assumption that any of these events starting within 7 days of an immunisation are at least possibly related. If the onset of the event is beyond 7 days, the event will be recorded on the adverse event CRF and a relationship determined by the investigator reviewing the event.

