##### 9.2.1.2 Safety

The primary **safety** endpoint is a grade 3 or above local or systemic clinical and laboratory solicited adverse event (see **section 7, Table 2**) or any grade of adverse event that results in a clinical decision to discontinue further immunisations.

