### 9.2.2.2 Safety

- Any grade of adverse event that occurs in a participant that has received at least one immunisation.

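### Section 9.5.3 takes worst severity and worst relationship separately, so by-relationship safety tables can show a grade 3 or above related event that no report supports

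*Protocol*

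**What the plan says.** Protocol section 9.5.3 sets a collapsing rule for coded adverse events. Its condition is "In all summaries, if a participant reports the same system organ class or preferred term more than once", and its consequence is "then the worst severity and worst relationship to trial vaccine will be taken". Nothing requires the two attributes to belong to one report.

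The same section then plans the presentation: "Safety outcomes will be reported overall with proportion and 95% confidence interval, and by group and time-point, and by relationship to study product".

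The outcomes presented in this way are partly severity thresholds. Section 9.2.1.2 defines the primary safety endpoint as a "grade 3 or above local or systemic clinical and laboratory solicited adverse event" or "any grade of adverse event that results in a clinical decision to discontinue further immunisations". The secondary outcome in 9.2.2.2 is "Any grade of adverse event that occurs in a participant that has received at least one immunisation".

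Relationship is assigned in two ways. Section 7.5.5 assumes, for solicited events, that "any of these events starting within 7 days of an immunisation are at least possibly related". If a solicited event begins after 7 days, it goes on the adverse event form and the investigator judges its relationship individually. Section 8.1 counts possibly, probably and definitely as related.

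**The concern.** Each maximum is right in its own table: worst severity in a severity table, worst relationship in a relationship table. The trouble comes when one collapsed record supplies both, as it would if a grade 3 or above outcome is broken down by relationship. The record can then describe an event that nobody reported.

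Take a participant with a grade 1 neutropenia found at a two-week follow-up visit and rated possibly related. Later the same participant has a grade 3 neutropenia rated unrelated. Both begin more than 7 days after an immunisation, so each was judged on its own. Under the rule the participant contributes one grade 3, possibly related neutropenia. At system organ class level the two reports need not even be the same condition.

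What is at stake is the description of severe events attributed to product. That matters here because section 7.6 describes the DNA with electroporation, and MVA-CMDR with the protein at the same timepoint, as first-time uses. Genuine severe related events are expected to be few, so a handful of false ones could change how a table reads.

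**Working it through.** **1. Does the text allow the two attributes to be mixed?** Yes. Section 9.5.3 names two worst values and applies the rule to all summaries.

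**2. Can related and unrelated reports coexist in one term or class?** Not among solicited events starting within 7 days, which are all taken as at least possibly related. They can among later events. Section 7.1 has safety bloods at every visit after baseline, and section 7.1.2 puts follow-up visits at 2 and 4 weeks after immunisation. Many laboratory onsets will therefore fall outside the 7-day window. Unsolicited events are also judged one by one (7.5.1, 7.5.8).

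**3. Which outputs use the mixed record?** The primary endpoint has no relationship criterion. Taking the worst severity does not change whether a participant has any grade 3 or above event, so the proportion tested is the same with or without the flaw. Only presentations by relationship are exposed.

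**4. How large could it be?** The protocol states no figure that depends on this rule and no event rates; every rate below is an assumption. Per participant and per term or class, let

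- u = probability of at least one unrelated severe report
- r = probability of at least one related non-severe report
- q = probability of at least one genuinely related severe report

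With independence, P(false severe related) = u × r × (1 − q). Group sizes of 60 (first randomisation) and 90 (second) are from section 9.3. The lower-reactogenicity arm is given r = 0.30, q = 0.01, and the higher one r = 0.60, q = 0.03. For u = 3% and n = 90: 90 × 0.03 × 0.30 × 0.99 = 0.80, and 90 × 0.03 × 0.60 × 0.97 = 1.57.

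| u | n = 60, lower vs higher | n = 90, lower vs higher |
|---|---|---|
| 1% | 0.18 vs 0.35 | 0.27 vs 0.52 |
| 3% | 0.53 vs 1.05 | 0.80 vs 1.57 |
| 5% | 0.89 vs 1.75 | 1.34 vs 2.62 |
| 10% | 1.78 vs 3.49 | 2.67 vs 5.24 |

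The genuine counts at n = 90 would be 90 × 0.01 = 0.9 and 90 × 0.03 = 2.7.

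**5. Check by simulation.** Five post-immunisation periods; unrelated background events 6% per period, 10% of them severe; 2% of related events severe. The related-event rate ρ per immunisation is varied.

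| ρ | Severe related, separate maxima | Severe related, same report | False |
|---|---|---|---|
| 5% | 1.2% | 0.5% | 0.66% |
| 10% | 2.2% | 1.0% | 1.2% |
| 20% | 3.9% | 2.0% | 1.9% |
| 40% | 6.6% | 4.0% | 2.6% |

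The closed form agrees: false = [(1 − 0.02ρ)^5 − (1 − ρ)^5] × [1 − (1 − 0.006)^5]. At ρ = 20% this is (0.980 − 0.328) × 0.0296 = 1.9%.

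**6. Does it always favour one arm?** No. The ratio of false rates between arms is r₂(1 − q₂) / [r₁(1 − q₁)].

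- r = 0.30 vs 0.60, q = 0.01 vs 0.03: 0.582 / 0.297 = 1.96
- equal r and equal q: 1.00
- r = 0.60 in both, q = 0.02 vs 0.45: 0.55 / 0.98 = 0.56
- r = 0.30 vs 0.60, q = 0.02 vs 0.60: 0.24 / 0.294 = 0.82

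**The case against.** The strongest reply is that the protocol draws no severity-by-relationship table. Table layout belongs to the statistical analysis plan, which is not at hand, and that plan could apply the rule within time-point or keep the two attributes in separate tables. This stands in part: the false cell is possible, not certain. But the rule is written into the protocol for all summaries, and outcomes are to be reported overall as well as by time-point. Presenting a grade 3 or above outcome by relationship is such a cross-classification in substance.

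A second reply is that solicited reactions are documented separately from other adverse events (section 8.2) and need not be pooled with them. That also stands. The frequent mild reactions in the first week may never enter the merge, which lowers r. Section 7.5.8 prefers a diagnosis to its symptoms, so a severe headache during malaria should be recorded as malaria and would not merge with an earlier headache term. Laboratory findings and unsolicited events still leave a route.

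Third, no decision depends on these tables. Expedited reporting (8.2) and the monitoring board's trigger (15.5) work on individual events, and the error overstates related severity instead of hiding it. This is correct and limits the importance.

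Two stronger readings are tempting. A reader might infer that the primary safety comparison is inflated; it is not, because section 9.2.1.2 uses no relationship criterion. A reader might also infer that the more reactogenic arm is always penalised. The protocol gives no rates by arm, and step 6 shows that the excess can vanish or reverse.

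**Conclusion.** The point holds in a limited form. Read as written, section 9.5.3 can place a participant in a grade 3 or above, related cell that no single report supports. The effect is confined to descriptive summaries by relationship.

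Its size cannot be derived from the protocol. With u from 1% to 10% and r from 0.30 to 0.60 it is roughly 0.2 to 5 participants per arm per term or class, assuming independence and merging over the whole trial. Merging within time-point would give less. The only nearby fact is in section 2.3: one grade 3 neutropenia, thought probably unrelated, among 40 protein-boosted participants of the preceding trial (1/40 = 2.5%). One event cannot fix u, but it shows that the needed kind of report occurs and makes the lower rows of the range more plausible than the upper.

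An excess in the more reactogenic arm follows only if mild related events differ between arms and genuine severe related events are rare. The mostly mild reactogenicity described in section 2.3 makes the second condition plausible; the first is unknown.

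**What to change.** In section 9.5.3, keep the worst severity over all reports for tables by severity alone. For any table of related events, or of severity by relationship, first restrict to reports rated possibly, probably or definitely related, then take the worst severity among those. State that severity and relationship are never combined from different reports. If such a table has a not-related column, build it in the same way from the remaining reports, so that an unrelated severe event still appears.

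False severe related records then number zero by construction, and every report that is itself both severe and related is kept. The cost is one sentence and minor programming, with no new data. The tabulated count of severe related events may be slightly lower than under the present rule.
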